**17a) Blinding:**

This study is unblinded after allocation of groups 7 and 8.

**17b) Circumstances permitting unblinding:**

N/A

**18a) Data collection methods:**

Standardised paper data collection forms are completed by dedicated, trained study staff at each visit. The data in these forms are then transcribed into OpenClinica, a computer-based data collection software package. Blood samples are collected by staff specifically trained in paediatric phlebotomy. The volume of blood collected and the site of venepuncture are recorded. The site of the vaccine administration is also recorded.

Parents are asked to complete an online or paper diary detailing reactogenicity for seven days following vaccine administration.

**18b) Plans to promote retention and complete follow up:**

Participants attending clinic will be given a small reimbursement for their travel costs and parking. Participants who receive home visits will not receive payments. Participants who miss clinic study visits will be offered a follow up visit at home if practicable.

**19) Data management:**

In this study, the paper CRF and eDiary entries will be considered source data. Data for analysis will be entered onto an electronic database or eCRF (OpenClinica or REDCap (Research Electronic Data Capture)). Other documents such as medical notes and GP letters may be used as source documents if required.

Access to Data

Direct access will be granted to authorised representatives from the Sponsor, host institution and the regulatory authorities to permit trial-related monitoring, audits and inspections.

Data Recording and Record Keeping

All study files with demographic and clinical details on the participants will be kept in a locked research office at Centre for Clinical Vaccinology and Tropical Medicine (CCVTM). The study data will be subsequently entered on to a computer with an electronic database protected by a password and encrypted transfer. All stored blood samples will be identified by study number only and will have no personal identifiers.

Information on study participants will be recorded on hard copy source documents held locally, and information will be entered into a web based electronic CRF (eCRF, OpenClinica™ or REDCap database stored on a secure server within the UK and has restricted access and is password-protected with accountability records).

**20a) Statistical methods:**

We have been limited in this study due to the number of participants vaccinated in previous trials as infants. Due to small sample sizes, the statistics will be descriptive, reported in the form of percentages, frequencies, geometric mean titers and geometric mean fold rises with 95% confidence intervals, per group and per strain (for the three strains: H44/76, 5/99, NZ98/254). For geometric mean titers and fold rises, data will be log transformed (base 10), and confidence intervals will be calculated on this log scale, prior to transforming back onto the original scale for reporting and interpretation. Confidence intervals for proportions will be calculated using the binomial exact method.

Primary objective

A descriptive analysis will be performed after all participants have completed visit 3 (day 180) in order to evaluate the primary endpoint of the study. This will be done by calculating the geometric mean of fold change in hSBA titre from Day 0 to Day 180, for each group for which this data is available.

Secondary objectives (For the six follow-on groups only)

To assess at Day 0 the persistence of the protective antibody response in adolescents after infant vaccination compared to adolescents after infant vaccination with toddler boosting, the following statistical parameters and their 95% confidence intervals will be determined as outlined above:

• Percentage of participants with an hSBA titre ≥ 1:4

• Geometric mean of hSBA titres

Exploratory objectives

At Days 0, 28, 180 and 365 post-treatment:

- the following statistical parameters and their 95% confidence intervals will be determined for each of the previously immunised groups, as outlined above:
  - Percentage of participants with an hSBA titre ≥ 1:4
  - Geometric mean of hSBA titres
- For B-cell memory and other immune cell types, summary statistics (Mean (SD) or Median (IQR), as determined by the distribution of the data) will be presented

Reactogenicity Analysis:

The frequency and severity of local and systemic solicited vaccine reactions will be summarised as frequencies and percentages for the participants overall for each dose of 4CMenB vaccine, separately for each treatment group.

**20b) Methods for any additional analyses:**

The principal comparisons will be performed on a per-protocol basis where the population for the immunogenicity analysis will consist of all participants who receive one or two doses of the vaccine (depending on the group) and providing at least one evaluable serum sample (after or before vaccination). An intention-to-treat analysis will also be performed where all participants will be included in the analysis if they are successfully vaccinated on Day 0. If a participant later withdraws from the study, data up until that point will be included in the analysis.

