**7) Objectives:**

Children who took part in previous 4CMenB trials are now approaching adolescence, and therefore we are presented with the unique possibility to specifically address the following questions:

1. What is the persistence of the protective antibody response and B-cell memory in adolescents 10 years after infant vaccination?
2. What is the persistence of protective antibody responses and B-cell memory among adolescents after infant vaccination with toddler boosting (eight years after the last 4CMenB vaccination)?
3. Is the protective antibody response to an adolescent booster among individuals immunised in early childhood higher and/or more persistent than in naïve adolescents?

Analysis of bactericidal activity (primary outcome).

The ability of the antibodies in participants’ serum samples to mediate killing of meningococci in the presence of complement (serum bactericidal activity (SBA)), will be quantified. The target strains in the SBA assay will be a panel of wild-type strains, in order to elucidate the antigen-specific SBA titre. The SBA titre will be calculated as the lowest concentration of the serum dilution giving a 50% reduction of colony forming units (CFUs) of a specified inoculum of bacteria after incubation with participant serum in the presence of complement.

Cellular responses and cytokine release (exploratory outcome).

Laboratory analyses to quantify the B- and T-cell responses specific to 4CMenB may be performed when feasible using peripheral blood mononuclear cells (PBMCs) and plasma derived from study participants sampled before, and after each vaccine dose, using the assays described below:

- Analyses of B cell responses: The ability of 4CMenB to stimulate a detectable increase in IgG, IgA and IgM producing antigen-specific memory B cells enumerated by ELISPOT using plates coated with vaccine antigens (OMVs, fHbp, NHBA, NadA and/or PorA). The phenotype and kinetics of the B-cell subsets involved in the response can be determined by flow cytometry. In addition, other assays to monitor the B-cell immune response to the vaccines may be performed if sufficient samples are available.

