**11a) Interventions for each group:**

All participants will be required to undergo four episodes of venepuncture as part of the immunogenicity analysis. All naïve participants (groups 7 and 8) will receive two doses of 4CMenB either on day 0 and 28 or day 0 and 365. All follow-on participants (groups 1-6) will receive one dose of 4CMenB on day 0.

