**12) Outcomes:**

Primary outcome:

Serum bactericidal activity against meningococcal strains at day 0 and 180 days post-immunisation, measured by validated assay.

Key secondary outcomes:

- Serum bactericidal activity before vaccination, measured at day 0.
- Serum bactericidal activity against meningococcal strains. Quantification and qualitative characterisation of B-cell memory and other immune cell types, measured at day 0, 28, 180 and 365 post-immunisation.
- Parental recording of eDiary information for 7 days post vaccination. Reactogenicity data gathered at all time points after vaccines given.

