**20c) How to deal with protocol non-adherence or missing data:**

All available data will be used in the analysis except that which is from participants excluded from the per-protocol populations. Missing data will not be imputed.

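### Both analysis sets require study vaccination, so a follow-on child bled on Day 0 but never dosed would drop out of the Day 0 persistence analysis, which is measured before the dose.

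*Protocol*

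**What the plan says.** **The endpoint.** The first objective in section 7 asks: "What is the persistence of the protective antibody response and B-cell memory in adolescents 10 years after infant vaccination". The second asks the same for children who also had a toddler booster. Section 20a turns the antibody part into a secondary analysis, restricted to the six follow-on groups: "To assess at Day 0 the persistence of the protective antibody response in adolescents after infant vaccination", set against infant vaccination with toddler boosting. The summaries are the percentage with an hSBA titre of at least 1:4 and the geometric mean titre, with 95% confidence intervals, by group and by strain. Section 12 fixes the timing: "Serum bactericidal activity before vaccination, measured at day 0". The study dose is due the same day (section 11a): "All follow-on participants (groups 1-6) will receive one dose of 4CMenB on day 0".

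**The analysis sets.** Section 20b describes the per-protocol population for immunogenicity as "all participants who receive one or two doses of the vaccine (depending on the group) and providing at least one evaluable serum sample (after or"; the bracket, cut short here, goes on to admit a pre-dose sample as well. It adds an intention-to-treat analysis in which "all participants will be included in the analysis if they are successfully vaccinated on Day 0". It then says: "If a participant later withdraws from the study, data up until that point will be included in the analysis".

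**The data-use rule.** Section 20c states: "All available data will be used in the analysis except that which is from participants excluded from the per-protocol populations". No other analysis set is defined in the protocol.

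**The concern.** A pre-dose titre carries full information about persistence whether or not the child goes on to be vaccinated. Requiring vaccination makes sense for post-dose titres and for change from Day 0. For the Day 0 result it makes inclusion depend on a later event that has no bearing on the measurement.

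What is at stake is precision. The follow-on pool cannot be enlarged: section 14 ties it to the 83 children who completed the earlier Oxford studies and expects about half to return. Section 20a itself gives small numbers as the reason for a purely descriptive analysis. A valid Day 0 serum from this pool cannot be replaced by recruiting someone else.

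The point concerns only the pre-dose result in groups 1-6. It does not touch the randomised naïve groups.

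**Working it through.** **Step 1: apply the rules to the case.** Take a child in groups 1-6 with an evaluable Day 0 serum who never receives the study dose.

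- Per-protocol set: a dose and at least one serum are both required. The child has the serum but not the dose, so is out. The words allowing a sample from before or after vaccination relax when the serum is taken, not the need for a dose.
- Intention-to-treat set: the child was not vaccinated on Day 0, so is out.
- Withdrawal sentence: it follows the Day 0 vaccination condition and speaks of someone who leaves later. It keeps the data of vaccinated children who withdraw and does not admit an unvaccinated one.
- Section 20c: the child is outside the per-protocol set, so the data are not used.

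The child therefore enters no Day 0 analysis.

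**Step 2: inputs for the size.** From the protocol: 83 previously immunised children plus 30 naïve gives the stated target of 113, which reproduces. About 50% of the 83 are expected to return, and there are six follow-on groups. There is no formal sample-size calculation and no SD to reproduce. Expected return is 0.5 × 83 = 41.5, about 42. Assuming an equal split, which the protocol does not state, 41.5 / 6 = 6.9, about 7 per group.

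**Step 3: geometric mean titre, one group.** The 95% half-width on the log10 scale, in units of the SD, is t(0.975, n−1) / √n.

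- n = 7: 0.925 SD
- n = 6: 1.049 SD
- Ratio: 1.049 / 0.925 = 1.13, about 13% wider after one loss. The ratio does not depend on the SD.

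**Step 4: percentage at or above 1:4, exact binomial as in section 20a.** The counts are illustrative values near one half.

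| Setting | Count | 95% CI | Width |
|---|---|---|---|
| One group, all kept | 4/7 | 0.184 to 0.901 | 0.717 |
| One group, one lost | 3/6 | 0.118 to 0.882 | 0.764 |
| Pooled, all kept | 21/42 | 0.342 to 0.658 | 0.316 |
| Pooled, one lost | 20/41 | 0.329 to 0.649 | 0.320 |

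One restored child moves a group percentage from 3/6 = 50% to 3/7 = 43% or 4/7 = 57%, about 7 points either way. Pooled, 20/41 = 48.8% becomes 20/42 = 47.6% or 21/42 = 50.0%, about 1.2 points.

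**Step 5: how many children.** The protocol does not say. With none, every effect above is zero.

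**The case against.** The strongest reply is that the case may never arise. The bleed and the single dose are both due on Day 0, the family has agreed to a booster trial, and known anaphylaxis to a vaccine component is already an exclusion. This stands, and it is why the point ranks low.

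Second, the affected group is narrow. The per-protocol wording does not say the dose must fall on Day 0, so a child bled then and dosed later could still qualify. A child who is vaccinated and then leaves is kept. Only a child who is never dosed is lost. This also stands.

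Third, a single vaccinated set keeps the Day 0 titres on the same children as the primary Day 0 to Day 180 fold change. That is a good reason to keep the requirement for fold changes, but not to apply it to a separate pre-dose endpoint that answers two objectives of its own.

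Fourth, objective-specific sets are often left to the SAP. Here, however, the protocol has already fixed a rule that does not fit one of its endpoints, and an SAP that follows it would inherit the mismatch.

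Fifth, section 20c read literally would also undercut the intention-to-treat analysis that 20b promises, so it may not be meant literally. Even without 20c, the child fails both sets in 20b.

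**Conclusion.** The point holds as a mismatch between a stated rule and a stated endpoint: the analysis sets condition a pre-dose result on receipt of the dose. If one child were affected, that child's group would lose about 13% in log10 interval half-width, given about 7 per group from an assumed equal split of about 42. Pooled over the follow-on groups the effect is negligible. The number of such children is not given and may be zero.

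Two stronger readings are not supported:

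- A reader might infer that Day 0 sera are in fact being discarded and that two of the three objectives are losing precision. Nothing in the protocol shows that any child is bled and not dosed. Larger widening would need two or more such children in the same small group, which is a worst case rather than an expectation.
- A reader might infer a material selection bias from restricting to children who go on to vaccination. Every enrolled follow-on child has already agreed to a trial in which all receive a dose, so enrolment itself imposes most of that selection and the fix would remove little of it.

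Severity is low: an improvement worth making because it costs almost nothing.

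**What to change.** Add to section 20b: *The Day 0 persistence analyses for groups 1-6 include every enrolled participant with an evaluable Day 0 serum, whether or not the study vaccine was then given, subject to consent to use the sample.* In section 20c, exempt this analysis from the per-protocol exclusion. Keep the vaccination requirement for post-vaccination time points and for Day 0 to Day 180 fold changes.

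The consent condition is needed because the protocol does not say what happens to the sample of a child who withdraws before dosing.

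The cost is one sentence and one cross-reference, with no new visits, samples or assays. It is best settled before the data are analysed, so that inclusion is not decided with results in view.

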**20c) How to deal with protocol non-adherence or missing data:**

All available data will be used in the analysis except that which is from participants excluded from the per-protocol populations. Missing data will not be imputed.

**21a) Data monitoring:**

Regular monitoring will be performed by CTRG (Clinical Trials and Research Governance), the study monitor, according to GCP.

The P.I. will submit (in addition to the expedited reporting above) DSURs once a year throughout the clinical trial, or on request, to the Competent Authority (MHRA in the U.K.), Ethics Committee, HRA (where required) and Sponsor.

**21b) Description of interim analyses and stopping guidelines:**

A descriptive analysis will be performed after all participants have completed visit 3 (day 180) in order to evaluate the primary endpoint of the study.

The Principal Investigator and Trial Safety Group will have the right to recommend termination of the study at any time on grounds of participant safety. If the study is prematurely terminated the investigator will promptly inform the participants. If the study is halted, the MHRA and relevant Ethics Committee will be notified within 15 days of this occurring.

**22) Harms:**

The Medicines for Human Use (Clinical Trials) Regulations contain a requirement for the notification of "serious breaches" to the MHRA within 7 days of the Sponsor becoming aware of the breach.

In the event that a serious breach is suspected the Sponsor must be contacted within 1 working day. In collaboration with the P.I., the serious breach will be reviewed by the Sponsor and, if appropriate, the Sponsor will report it to the REC committee, Regulatory authority within seven calendar days.

**23) Auditing:**

N/A

**24) Research ethics approval:**

This trial has been approved by Nottingham 2 Research Ethics Committee (reference 17/EM/0466).

**25) Protocol amendments:**

Protocol amendments will be communicated to relevant parties via email or phone call as necessary.

**26a) Consent or assent:**

A written version and verbal explanation of the study information leaflet and informed consent will be presented to the parent/legal guardian of the participant and the participant detailing:

- the exact nature of the trial.
- the implications and constraints of the protocol.
- the known side effects and any risks involved in taking part.
- Sample handling – participants will be informed that anonymised samples taken during the course of study may be shared with study collaborators, including collaborators outside of the European Union, for the purposes of this study.

It will be clearly stated that the participant is free to withdraw from the trial at any time for any reason without prejudice to future care, without affecting their legal rights and with no obligation to give the reason for withdrawal.

Written informed consent/assent will be obtained by means of dated signatures of both the parent/participant and of the person who presented and obtained the informed consent/assent. The person who obtained the consent must be suitably qualified and experienced and have been authorised to do so by the Principal Investigator. A copy of the signed informed consent/assent forms will be given to the parent. The original signed forms will be retained at the trial site.

**26b) Ancillary studies:**

The parent/legal guardian of the participant will also be informed that their samples would be eligible for BioBank (Oxford Vaccine Centre Biobank 2009/09, Oxford Vaccine Centre Biobank Ethics Ref: 16/SC/0141)**.** Separate consent/assent is sought for this. Biobank is optional.

**27) Confidentiality:**

The trial staff will ensure that the participants’ anonymity is maintained. The participants will be identified only by a participant ID number on all trial and source documents and any electronic database, with the exception of the paper CRF, where participant initials may be added. All documents will be stored securely and only accessible by trial staff and authorised personnel. The trial will comply with the GDPR, which requires data to be anonymised as soon as it is practical to do so.

**28) Declaration of competing interests:**

[name] reports grants from Okairos, and Pfizer, which finished within the past 36 months outside the submitted work. [name] is Chair of UK Dept. Health’s Joint Committee on Vaccination & Immunisation & the EMA scientific advisory group, on vaccines and is a member of the WHO’s SAGE.

**29) Access to data:**

Direct access will be granted to authorised representatives from the Sponsor, host institution and the regulatory authorities to permit trial-related monitoring, audits and inspections.

**30) Ancillary and post-trial care:**

There will not be provision of 4CMenB vaccine beyond the trial period.

The University of Oxford has a specialist insurance policy in place which would operate in the event of any participant suffering harm as a result of their involvement in the research (Newline Underwriting Management Ltd, at Lloyd’s of London).

**31a) Dissemination policy:**

The Investigators will co-ordinate dissemination of data from this study. All publications (e.g., manuscripts, abstracts, oral/slide presentations, book chapters) based on this study will be reviewed by each sub-investigator prior to submission. Authors will acknowledge that the study was funded by the Meningitis Research Foundation and NIHR Oxford Biomedical Research Centre. Trial participants will be notified of the results of the study upon publication of the study.

**31b) Authorship eligibility and use of professional writers**

Authorship will be determined in accordance with the ICMJE (International Committee of Medical Journal Editors) guidelines and other contributors will be acknowledged. There is no intention to utilise professional writers.

**31c) Plans for granting public access to the full protocol, participant-level dataset, and statistical code**

The datasets used and/or analysed during the current study are available from the corresponding author on reasonable request.

